### Sampling

Table 2 summarizes the sample size requirements by activity, along with underpinning assumptions. To determine changes in RMNCH knowledge, practices, and careseeking over time (study aim 1), sampling will be powered to detect changes in coverage across study arms. To detect a 5% difference in reported practice of exclusive breastfeeding assuming an alpha of 0.05, 80% power, the estimated sample size for a two-sample proportions test would be 3200 women. After adjusting for a design effect (variance inflation factor) of 1.25 due to clustering at the level of the Community Development Block and a 20% loss to follow-up from enrollment to endline surveys and a potential loss of 35% of women due to poor reporting of phone numbers and/or changes to original phone numbers provided, a total of 5000 women will be enrolled to the study. Assuming 40% of women have access to a mobile phone, we anticipate that nearly 700,000 households will be listed in all four districts of MP.

**Table 2 Tab2:** Sample size estimates by study aim

Study aim	Survey	Target population	Sample size	Assumptions
Study aim 1a*	Face to face survey to measure changes in infant feeding practices	Women 5–7 months pregnant in four districts of MP	5000	• 5% change in reported practice of immediate and exclusive breastfeeding • Loss to follow-up of 20% from enrolment to final follow-up visit • Variance inflation factor of 1.25
Study aim 1b	Phone survey to measure changes in infant feeding	Postpartum women randomized to Kilkari	5000	Descriptive survey; administered to all women enrolled into the study
Study aim 1c*	Test-retest	Women 5–7 months pregnant in four districts of MP	168 women to be interviewed twice	• Proportion of positive responses of 0.35 for rater 1 and 0.40 for rater 2 • Adjusting for a 15% loss to follow-up/refusal between the first and second surveys
Study aim 1*	Phone survey for postpartum women: infant feeding, essential newborn care, RMC during childbirth	Women 1–4 months postpartum in two districts of MP	880 women interviewed as part of face to face surveys contacted to yield 146 completed face to face and phone survey interviews	• 20% phone survey response rate • Proportion of positive responses of 0.35 for rater 1 and 0.40 for rater 2

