Study aim 2*	Phone survey for pregnant women: RMC during pregnancy	Women 5–7 months pregnant in four districts of MP	880 women interviewed as part of face to face surveys contacted to yield 146 completed face to face and phone survey interviews	• 20% phone survey response rate • Proportion of positive responses of 0.35 for rater 1 and 0.40 for rater 2
Study aim 2	MCTS/RCH registration	• FLHWs • Block and district medical officers • Data entry officers	64 in-depth interviews, 24 focus group discussions, and 24 observations	
Study aim 4	User perceptions of Kilkari	• FLHWs: ASHAs, ANMs • Women enrolled to Kilkari and male phone owners	49 in-depth interviews and six focus group discussions	

*Sample estimates based on kappa of 0.80, alpha of 0.05, margin of error of 0.05%

Among pregnant women, a module on RMC during antenatal care will be integrated into the baseline assessment amongst the enrolled women. To measure RMC during childbirth, a total of 880 women with a birth outcome in the preceding 1 to 4 months will be interviewed. This sample size was designed to accommodate inter-modal testing and is sufficient to additionally measure the prevalence of the RMC indicator of reported verbal abuse during childbirth with 80% power, alpha of 0.05, and precision of 5%.

To generate validated phone survey tools for RMC, we will aim to determine the inter-modal reliability of face to face versus computer-assisted telephone interviewing (CATI)/phone surveys for both pregnant and postpartum women. Assuming a kappa of 0.80, a margin of error of 0.05, an alpha of 0.05, and the proportion of positive responses of 0.35 for rater 1 and 0.40 for rater 2, 146 participants who have completed the survey are required. Adjusting for a 20% loss to follow-up between the face to face women’s survey and the following mobile phone survey, and a 20% baseline completion percentage for the latter, 880 women with a birth outcome in the preceding 1 to 4 months will be interviewed face to face. Within 1–2 weeks of the initial interview, a random sample of those completing the face to face interview who consent to be called for the follow-up phone survey will be contacted. Assuming a 20% response rate, all 880 women will be contacted as part of the phone survey to yield the 146 completed face to face and phone survey interviews.

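### The reliability sub-study's 146 completed pairs give a 95% margin of about ±0.10 on kappa, not the stated 0.05, which would need about 585 pairs

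*Protocol article*

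**What the plan says.** The Sampling section of the protocol article plans the comparison of face to face and phone interviews by the precision of kappa. Its precision inputs read "Assuming a kappa of 0.80, a margin of error of 0.05, an alpha of 0.05". It further takes positive answers to make up 0.35 of the first rating and 0.40 of the second. From these it concludes that "146 participants who have completed the survey are required". The Table 2 footnote repeats the inputs as "Sample estimates based on kappa of 0.80, alpha of 0.05, margin of error of 0.05", with a percent sign directly after the last figure.

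Two recruitment targets go with this. For the inter-modal comparison, the text starts from "Adjusting for a 20% loss to follow-up between the face to face" interview and the phone survey, adds a 20% completion percentage for the phone survey, and arrives at 880 women. It closes by assuming a 20% response rate, under which "all 880 women will be contacted as part of the phone survey to yield the 146 completed face to face and phone survey interviews". For the test-retest comparison, Table 2 plans "168 women to be interviewed twice", with the note "Adjusting for a 15% loss to follow-up/refusal between the first and second surveys" and the same positive proportions.

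**The concern.** The article prints every input to the calculation as well as its result, so the result can be checked, and it does not follow. The half-width of an interval for kappa shrinks with the square root of n, so a margin wrong by a factor of 2 means a sample size wrong by a factor of 4. At stake is the precision claimed for the agreement estimates that feed the phone tool. According to the Measurement section (Study aim 1), that tool is later administered to the trial women at 1–4 months postpartum. A reader who relies on the planning text would expect agreement to be known twice as precisely as the design allows.

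**Working it through.** **Inputs** (Sampling section): kappa κ = 0.80; positive proportions p1 = 0.35 and p2 = 0.40; alpha 0.05. The article does not say whether alpha is one- or two-sided. I take a two-sided 95% interval (z = 1.96) and read the margin of error as its half-width d.

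**Implied table**
- Chance agreement: pe = 0.35 × 0.40 + 0.65 × 0.60 = 0.53.
- Observed agreement: po = pe + κ(1 − pe) = 0.53 + 0.80 × 0.47 = 0.906.
- Cells: both positive (0.906 − 1 + 0.35 + 0.40)/2 = 0.328; discordant 0.35 − 0.328 = 0.022 and 0.40 − 0.328 = 0.072; both negative 0.578.

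**Variance of kappa** (Fleiss-Cohen-Everitt): Q/n, with Q = (A + B − C)/(1 − pe)⁴.
- A = 0.328 × (0.47 − 0.75 × 0.094)² + 0.578 × (0.47 − 1.25 × 0.094)² = 0.12417
- B = 0.094² × (0.022 × 1.05² + 0.072 × 0.95²) = 0.00079
- C = (0.906 × 0.53 − 2 × 0.53 + 0.906)² = 0.10639
- Q = 0.01856/0.04880 = 0.3804

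**Sample size**, n = z²Q/d²
- Reproducing the plan's figure: d = 0.10 gives 1.96² × 0.3804/0.0100 = 146.1, which matches 146.
- As stated: d = 0.05 gives 1.96² × 0.3804/0.0025 = 584.6, so 585.
- Footnote taken literally: d = 0.0005 is 100 times smaller than 0.05, so n is 10,000 times larger, about 5.8 million. This is plainly a slip of units.

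**Precision at n = 146**: 1.96 × √(0.3804/146) = 0.100, or 0.70 to 0.90 around 0.80. A simulation of 200,000 tables gave a half-width of 0.101 and a central 95% range of 0.69 to 0.90. At 584 pairs it gave 0.050.

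**Other readings of 0.05**

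| Reading | Pairs needed |
|---|---|
| One-sided z | 412 |
| Simple variance po(1 − po)/(1 − pe)² | 592 |
| Common-correlation variance, prevalence 0.35 to 0.40 | 578 to 612 |
| Variance under zero kappa | 1,519 |
| Power-based forms, difference 0.05 | 941 or more |
| 0.05 as a standard error | 152 |

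None gives 146. Only the last comes close, and a standard error is not a margin of error.

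**The target of 880**
- Probable origin: 146/0.20 × 1.20 = 876, rounded up.
- Both 20% figures multiplied: 880 × 0.80 × 0.20 = 141 pairs, half-width 0.102.
- Response rate alone: 880 × 0.20 = 176 pairs, half-width 0.091.

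**The target of 168**: 146 × 1.15 = 167.9, so it appears to start from 146. After a 15% loss, 168 × 0.85 = 143 pairs, half-width 0.101.

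**The case against.** The core arithmetic has no good answer, but four limits are fair.

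First, the article shows only that 0.05 and 146 are incompatible, not which one is the mistake. That stands as a matter of logic. The match at 0.10 makes a misreported margin much the likelier explanation, but the authors must confirm it.

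Second, a reader might infer that both recruitment targets are also too small, because the losses seem to have been added to n instead of divided out. The documents do not support this as a firm statement. For 880 the shortfall (141 against 146) arises only if both 20% figures apply. Table 2 and the closing sentence of the Sampling text name only the response rate, which gives 176, more than enough. For 168, Table 2 states no required number of pairs; 146 is inferred from the shared inputs, and the half-width moves only from 0.100 to 0.101.

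Third, a reader might infer that the tools would be declared validated on a margin twice as wide as claimed. The article gives no threshold or decision rule for kappa. The only numeric cutoff for the phone tools, under Phone surveys, is a Cronbach's alpha of 0.7. Any interval reported with the results will also show its true width.

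Fourth, the article describes the sub-study only in brief and refers elsewhere for detail. That would excuse an omission, but the point here is a printed result that disagrees with its printed inputs.

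**Conclusion.** The point holds for the margin of error. The stated precision is too favourable by a factor of 2, and the stated margin would need about four times the pairs (585 against 146). This rests on a two-sided 95% interval and on reading the margin as its half-width; a one-sided reading still needs 412. The percent sign in the footnote is a further inconsistency.

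The derivation of 880 is inconsistent between its two sentences (141 or 176 pairs, neither being 146), but the effect on precision is small either way. The test-retest difference is negligible.

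None of this bears on the randomized comparison. The footnote's asterisk also stands on the Table 2 row for the 5000 women, from which a reader might infer that the main sample is affected. The Sampling text derives that number from a comparison of two proportions, with no kappa involved. The right weight is a correction that should be made, in a secondary component.

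**What to change.** Keep 146 completed pairs and restate the margin of error as ±0.10 in the Sampling text and the Table 2 footnote, removing the percent sign. If ±0.05 really was the aim, say that it needs about 585 pairs and that the design does not deliver it.

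State whether the 20% loss to follow-up and the 20% phone completion are separate losses, and give the expected number of pairs to match: about 141 if both apply, 176 if only the response rate does. For test-retest, an expected 143 pairs can be noted; the target need not change.

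The cost is wording only, with no added recruitment, and a less favourable stated precision. Pursuing ±0.05 would be another matter: 585/0.85 = 689 test-retest women, and between 585/0.20 = 2,925 and 585/(0.80 × 0.20) = 3,657 face to face interviews, depending on which losses apply.

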### Measurement

Figure 2 provides an overview of enrolment and study design over time and the Standard Protocol Items: Recommendations for Interventional Trials (SPIRIT) are presented in Fig. 3 and Additional file 1. At enrollment, women will be administered a survey containing modules on phone ownership, geographical and demographic characteristics, knowledge (danger signs during pregnancy, delivery, and postpartum; essential newborn care; nutrition; hygiene, diarrhea treatment, family planning, etc.), practices (immediate, early, and exclusive breastfeeding; complementary feeding; skin-to-skin care, etc.), RMC, and coverage for antenatal care, delivery, and postnatal care. Around 6–8 weeks after the expected date of delivery, a phone survey will be administered to a random sample of the enrolled women until a target sample size of 3500 is attained (1750 each in intervention and control arms) to assess breastfeeding and newborn care practices. An endline survey will be carried out from November 2019 to February 2020 and each woman will be followed up at 12 months postpartum based on their expected date of delivery at enrollment. The endline survey will capture data on practices during pregnancy and intrapartum and postpartum periods.

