### Trial enrollment

Trial inclusion will be restricted to women who are 12–34 weeks of gestation at randomization, ≥ 18 years of age, speak and understand Hindi, and own or have access to a mobile phone during the morning and afternoon. Women will be excluded who are BSNL mobile subscribers (due to poor network coverage) and do not provide consent to participate in the trial.

To identify eligible women, all FLHWs in the study villages will be contacted to obtain a list of the currently pregnant women in their village. If the FLHW is not available, a census of those villages will be carried out to find women greater than 18 years of age, within the fifth to seventh month (12–34 weeks of gestation at randomization) of their pregnancy. Women who complete the face to face survey and consent to receive Kilkari messages will be randomized to receive Kilkari calls (intervention) or not receive messages (comparison). Intervention area participants will start to receive Kilkari calls by no later than 8 months (34 weeks) after conception. The timing of this enrolment is intended to mirror that observed in other state deployments of Kilkari which rely on the identification of pregnant women via the MCTS/RCH database and in practice therefore enroll women in the later stages of pregnancy and/or early postpartum.

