### Allocation and randomization

Gestational age, parity, age of woman, and ownership of phone are important variables potentially associated with exposure (listening to messages) and are likely to influence outcomes. The sample will be stratified by the above variables to allow for equal numbers of these categories in the sample between intervention and control groups (balance of covariates in the sample). Randomization will be performed using the *sample* command in stata with the use of the above listed variables as stratifiers. The randomization procedure will be done in blocks (block randomization) after the enrollment is completed for each sub-district administrative unit called as Community Development Block. This is to ensure a similar number of intervention and control subjects for each Community Development Block.

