#### Study aim 1: Generate evidence on the effectiveness of Kilkari in four districts of MP

Knowledge attitudes and practices (KAP) surveys will be administered at baseline and endline containing modules on phone ownership, geographical and demographic characteristics, knowledge (danger signs during pregnancy, delivery, and postpartum; essential newborn care; nutrition; hygiene, diarrhea treatment, family planning, etc.), practices (immediate, early, and exclusive breastfeeding; complementary feeding; skin-to-skin care, etc.), RMC, and coverage for antenatal care, delivery, and postnatal care. Questions on exposure to and sources for health information content will additionally be asked to identify possible sources of contamination. The list of individuals randomized to receive Kilkari content will be provided to BBC Media Action for enrollment into Kilkari continuously throughout the implementation of the baseline survey. Following 11–12 months, participants from both study arms will be interviewed as part of the face to face endline survey.

A phone survey will be administered to all study arm participants on a rolling basis at 1 month postpartum to measure RMNCH practices, including infant feeding practices and essential newborn care as well as RMC. Methods to generate a validated phone survey tool are described elsewhere and in brief will include a face to face survey administered to women during pregnancy and with a live birth outcome in the preceding 1–4 months postpartum at the time of the household listing. A sub-sample of respondents from the initial face to face survey will be administered a second test-retest survey by a separate but similar profile of enumerator. Findings from the face to face surveys will be used to generate phone survey tools which will be implemented amongst a random sample of pregnant and postpartum women who consent to be called for the follow-up phone survey. Analyses to assess the intermodal reliability of face to face versus phone survey responses will be used to generate a validated tool. The tool developed for postpartum women will subsequently be administered to women enrolled into the iRCT during pregnancy at 1–4 months postpartum (Fig. 2).

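### The November–February endline is shorter than the spread of due dates that eligibility allows, so not every woman can be interviewed at 12 months postpartum and the 1-year contraception outcome will mix postpartum ages

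*Protocol article*

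**What the plan says.** The Measurement section of the protocol article makes two commitments about the endline in one sentence, the first by calendar and the second for the individual woman: "An endline survey will be carried out from November 2019 to February 2020 and each woman will be followed up at 12 months postpartum". The second is counted from her due date as estimated when she enrolled. The Analyses section relies on the second: the primary analysis is to follow once all participants have reached 1 year postpartum, and adoption of modern contraception at that time is a primary outcome. The text gives no tolerance around 12 months.

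Three other sections bear on whether both can be met:

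- Trial enrollment: "Trial inclusion will be restricted to women who are 12–34 weeks of gestation at randomization". The next paragraph describes the same range as "within the fifth to seventh month (12–34 weeks of gestation at randomization) of their pregnancy", and Table 2 (Sampling) gives the target population as "Women 5–7 months pregnant in four districts of MP".
- Allocation and randomization: randomization takes place "after the enrollment is completed for each sub-district administrative unit called as Community Development Block", so it is staggered over calendar time.
- Measurement, study aim 1: "Following 11–12 months, participants from both study arms will be interviewed as part of the face to face endline survey". The starting point of those months is not named.

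**The concern.** A visit fixed to each woman's due date needs a field period at least as long as the range of due dates, less whatever tolerance is allowed. Here the field period is fixed by calendar and looks shorter than the range that eligibility permits, before staggered randomization is counted.

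At stake is what the contraception outcome means. If some women are interviewed before 12 months and others after, the analysis estimates use at a mixture of postpartum ages, while the plan and any report would call it use at 1 year. Women seen early have also not finished a message schedule that runs to 12 months postpartum, and family planning is its largest content area (16% in Table 1). The planned adjustment for gestational age at enrollment does not fully capture this: once enrollment is staggered, women of the same gestational age have different due dates and so different intervals to a fixed calendar window.

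**Working it through.** The documents state no figure for the share of women seen at 12 months, so there is none to reproduce.

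**Inputs from the protocol.** Endline November 2019 to February 2020; gestational age 12–34 weeks at randomization; visit at expected delivery date plus 12 months; randomization staggered by Community Development Block.

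**Assumptions.** Term of 40 weeks; window read at its widest; window placed as favourably as possible; gestational-age distribution and enrolment duration varied, because the text gives neither.

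**Step 1, window.** 1 November 2019 to 29 February 2020 is 30 + 31 + 31 + 29 = 121 days; 121/7 = 17.3 weeks.

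**Step 2, due dates from eligibility.** Due dates fall 40 − 34 = 6 to 40 − 12 = 28 weeks after randomization, a spread of 22 weeks. The shortfall is 22 − 17.3 = 4.7 weeks.

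**Step 3, size of the miss with one-day randomization.** With a centred window, 4.7/2 = about 2.4 weeks at each end; if all on one side, 4.7 weeks. For illustration, randomizing everyone on 1 September 2018 gives due dates from 13 October 2018 to 16 March 2019, and both ends reach 12 months more than two weeks outside the window.

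**Step 4, share of women outside, no tolerance.** With one-day enrolment and uniform gestational age over *w* weeks, the share is (*w* − 17.3)/*w*, or zero if *w* is below 17.3. With uniform gestational age and uniform enrolment over *A* weeks, each tail beyond a centred window has length *t* = (*w* + *A* − 17.3)/2 and the share outside is *t*²/(*wA*). For *w* = 22 and *A* = 13, *t* = 8.86 and the share is 78.5/286 = 27.4%. The triangular and normal rows were simulated.

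| Gestational age assumed | One day | 13 weeks | 26 weeks |
|---|---|---|---|
| Uniform, 12–34 weeks | 21.4% | 27.4% | 41.2% |
| Triangular, 12–34 weeks, peak 23 | 4.6% | 14.7% | 36.6% |
| Truncated normal, mean 24, SD 5 | 5.5% | 15.1% | 36.7% |
| Truncated normal, mean 24, SD 4 | 2.3% | 11.1% | 35.3% |
| Uniform, fifth to seventh month (17.4–30.4 weeks) | 0% | 11.2% | 34.9% |
| Uniform, completed months 5–7 (21.7–30.4 weeks) | 0% | 4.3% | 33.5% |

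A stress case with all women at 12–16 or 30–34 weeks gives about 50% in every column. Nothing in the protocol suggests such recruitment and it is left out of the range quoted, but it shows that the table is not an upper bound.

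**Step 5, effect of a tolerance.** For uniform 12–34 weeks, ±2 weeks reduces the three columns to about 3%, 17% and 31%; ±4 weeks reduces them to 0%, 8% and 23%.

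**Step 6, consistency of wording.** The fifth to seventh month spans about 13 weeks (8.7 weeks if read as completed months), not the 22 weeks of 12–34. The narrower readings fit the window only if enrolment takes no more than about 17.3 − 13 = 4 weeks, or 17.3 − 8.7 = 8.6 weeks.

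**The case against.** The strongest reply is that this is a matter of wording and visit tolerance. The protocol repeatedly describes its target as women in months five to seven, so 12–34 weeks may be only an outer bound. Under the narrower reading and quick enrolment, everyone fits. Enrolment timing is referred to Fig. 2, which is not shown, so the 13- and 26-week durations are scenarios and not findings. Visit tolerances are often left to the full protocol or analysis plan. From eligibility alone the miss is small: 2.4 weeks is two or three of 72 weekly calls, and only women seen early lose any. Randomization within block, stratified by gestational age, should make timing similar in both arms.

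Most of this stands, and it limits the point. A reader might infer that at least a fifth of women are measured at the wrong time. The documents do not support that: 21.4% requires uniform gestational age over the whole range and zero tolerance, and mid-peaked ages with one-day randomization give about 2–6%. A reader might also infer a biased comparison between arms; the stratified randomization argues against it. Nor is the 11–12 month statement a proven contradiction, since its starting point is not named and it may be an approximate window.

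The reply does not remove the inconsistency. The same article sets eligibility at 12–34 weeks, fixes the field dates and commits to 12 months for each woman. One-day randomization is the case most favourable to the plan, and the allocation procedure rules it out.

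**Conclusion.** The point holds in a limited form. A 17.3-week endline cannot reach every woman at 12 months after her expected delivery date when eligibility alone spreads due dates over 22 weeks. The 4.7-week shortfall needs no distributional assumption; it follows from the stated dates and the stated range.

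The number of women affected cannot be fixed from the text. With no tolerance and a best-placed window, the table supports about 0–21% for instantaneous enrolment, 4–27% for 13 weeks and 34–41% for 26 weeks. The problem is small if enrolment was short and gestational ages were narrow or mid-peaked. With about six months of enrolment, roughly a third or more fall outside under every assumption in the table, and the misses grow beyond the 2–5 weeks that eligibility alone produces.

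The consequence is a blurred 1-year contraception estimand and possibly slight dilution from women seen before the message course ends. The documents give no basis for putting a number on that dilution or for claiming confounding.

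**What to change.** Schedule each endline interview at expected delivery date plus 12 months within a stated tolerance, and set the field dates so that the earliest and latest due dates both fall inside it. This costs protocol wording and perhaps a longer, thinner field period.

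If November to February cannot move:

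- restate the outcome as use of modern contraception at about 12 months postpartum, and report the achieved range of interview times by arm;
- adjust for time from expected delivery date to interview;
- add a sensitivity analysis limited to women interviewed within the tolerance, at the cost of some precision.

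Reading status at an earlier common age from the adoption dates planned for the Cox model is not an adequate substitute. Adoption dates do not give current use unless discontinuation dates are also collected, and an earlier age would change the stated 1-year outcome.

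In either case, reconcile 12–34 weeks with the fifth-to-seventh-month description (Trial enrollment and Table 2), and 12 months postpartum with the 11–12 month statement under study aim 1, naming the latter's starting point.
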